## Abstract

Introduction: Cardiogenic shock due to myocardial infarction or heart failure entails a reduction in end organ perfusion. Patients who cannot be stabilized with inotropes and who experience increasing circulatory failure are in need of an extracorporeal mechanical support system. Today, small, percutaneously implantable cardiac assist devices are available and might be a solution to reduce mortality and complications. A temporary, ventricular, continuous flow propeller pump using magnetic levitation (Impella^®^) has been approved for that purpose. Methods and Study Design: JenaMACS (Jena Mechanical Assist Circulatory Support) is a monocenter, proof-of-concept study to determine whether treatment with an Impella CP^®^ leads to improvement of hemodynamic parameters in patients with cardiogenic shock requiring extracorporeal, hemodynamic support. The primary outcomes of JenaMACS are changes in hemodynamic parameters measured by pulmonary artery catheterization and changes in echocardiographic parameters of left and right heart function before and after Impella^®^ implantation at different support levels after 24 h of support. Secondary outcome measures are hemodynamic and echocardiographic changes over time as well as clinical endpoints such as mortality or time to hemodynamic stabilization. Further, laboratory and clinical safety endpoints including severe bleeding, stroke, neurological outcome, peripheral ischemic complications and occurrence of sepsis will be assessed. JenaMACS addresses essential questions of extracorporeal, mechanical, cardiac support with an Impella CP^®^ device in patients with cardiogenic shock. Knowledge of the acute and subacute hemodynamic and echocardiographic effects may help to optimize therapy and improve the outcome in those patients. Conclusion: The JenaMACS study will address essential questions of extracorporeal, mechanical, cardiac support with an Impella CP^®^ assist device in patients with cardiogenic shock. Knowledge of the acute and subacute hemodynamic and echocardiographic effects may help to optimize therapy and may improve outcome in those patients. Ethics and Dissemination: The protocol was approved by the institutional review board and ethics committee of the University Hospital of Jena. Written informed consent will be obtained from all participants of the study. The results of this study will be published in a renowned international medical journal, irrespective of the outcomes of the study. Strengths and Limitations: JenaMACS is an innovative approach to characterize the effect of additional left ventricular mechanical unloading during cardiogenic shock via a minimally invasive cardiac assist system (Impella CP^®^) 24 h after onset and will provide valuable data for acute interventional strategies or future prospective trials. However, JenaMACS, due to its proof-of-concept design, is limited by its single center protocol, with a small sample size and without a comparison group.

## 1. Introduction

Cardiogenic shock is characterized as a life-threatening, clinical syndrome that may present as an acute illness or an acute exacerbation of a chronic process. Acute myocardial infarction is the most common cause of this primary cardiac disorder and main cause of death [1,2]. Affected patients are critically ill and show inadequately low cardiac output that leads to circulatory failure with clinical and biochemical evidence of end-organ hypoperfusion, tissue hypoxia and consecutive or simultaneous malfunctions of vital organs [3].

The fundamental pathophysiological aspect of cardiogenic shock is a profound depression of myocardial contractility, ineffective cardiac stroke volume and failed circulatory compensation that perpetuate a vicious, downward spiral of reduced cardiac output, low blood pressure, low coronary perfusion and, eventually, further impairment of contractility [3].

A normal heart has a trapezoidal ventricular pressure-volume loop depending on ventricular preload and afterload [3]. Cardiogenic shock shows a restrictive patter with increased preload, afterload, end-diastolic pressure and low stroke volume leading to an increase in myocardial oxygen consumption [4]. Compensatory physiologic mechanisms allow transient stabilization of hemodynamics, but these mechanisms become pathological over time and lead to shock progression [3].

Clinically, this presents as hypotension refractory to volume resuscitation requiring further therapy intensification [5]. Multiorgan failure is common and long-term survival shows poor outcomes [6].

About 140,000 patients develop myocardial infarction every year in Germany [7]. Of these, approx. 10,000 patients (5–8%) develop cardiogenic shock [8]. Mortality of patients with cardiogenic shock due to myocardial infarction or heart failure remains very high with rates of 30–70% [8,9,10,11,12,13]. While recommended in current guidelines as a means for short term mechanical circulatory support (MCS, level of recommendation IIa, level of evidence C), there is a lack of evidence from randomized trials for cardiac assist devices in cardiogenic shock [14]. Available devices impact the circulatory system in distinct ways affecting preload, afterload, and contractility [15].

Aggressive treatment with inotropes and vasopressors has the potential to exacerbate the downward spiral of shock and results in higher myocardial oxygen consumption, increased afterload and impaired microcirculation [16].

The largest randomized trial of MCS in patients with CS, IABP Shock II, did not show any advantage of mechanical cardiac support using intra-aortic balloon counter-pulsation (decrease in afterload without active unloading of the failing left ventricle) compared to a conservative medical strategy of shock treatment [17]. Implantation of mechanical assist devices such as veno-arterial extracorporeal membrane oxygenation (VA-ECMO) is currently the only therapeutic option for stabilizing refractory cardiac shock patients [17,18,19]. However, due to the invasiveness of the procedure, there is a risk of bleeding, stroke, infections, sepsis, and limb ischemia [1]. In addition, VA-ECMO increases left ventricular end-diastolic pressure as well as afterload that again leads to increased wall stress and myocardial oxygen demand [20].

In contrast, Impella^®^ is a mechanical unloading device through placement in the left ventricle with continuous blood flow from the left ventricular cavity to the ascending aorta. It has been approved for the stabilization of patients with cardiogenic shock. It facilitates unloading of the left ventricle to support contractility independently from heart function and rhythm via adjustable flow rates. A dissociation of left ventricular peak pressure from aortic pressure can be achieved with higher mean arterial pressure. The pressure-volume loop of the left ventricle is shifted leftwards resulting in a lower left ventricular end diastolic pressure, a diminished pressure-volume area, lower left atrial and pulmonary wedge pressure, decreased myocardial oxygen consumption, and a reduction in the left ventricular wall tension [4]. Nevertheless, no study has systematically analyzed markers of myocardial unloading using Impella^®^ in patients with cardiogenic shock.

## 2. Methods and Analysis

### 2.1. Study Design

JenaMACS (Jena Mechanical Assist Circulatory Support) is a monocenter, prospective, open-labeled, proof-of-concept register study. JenaMACS will assess the impact of the Impella CP^®^ assist device on acute and subacute hemodynamic effects after implantation in patients with cardiogenic shock in addition to standard medical therapy. Figure 1 shows the study flow.

### 2.2. Patient and Public Involvement

Patients or the public were not involved in the design, or conduct, or reporting, or dissemination plans of our research.

### 2.3. Study Population

JenaMACS includes critically ill patients with cardiogenic shock and indication for an extracorporeal, mechanical, circulatory assist device determined by corresponding PAC (pulmonary artery catheter) hemodynamics (mean arterial pressure (MAP), pulmonary wedge pressure (PCPW), pulmonary artery pressure (PAP), pulmonary vascular resistance (PVR), systemic vascular resistance (SVR), mixed venous oxygen saturation (mvO2Sat), SV (stroke volume)). Inclusion and exclusion criteria are listed in Table 1.

### 2.4. Screening

All patients referred to our department with cardiac shock requiring hemodynamic support via an MCS device and that are eligible for Impella CP^®^ implantation will be screened.

### 2.5. Obtaining Informed Consent

The nature, aim and full extent of study participation are explained to each subject (or legally authorized representative or independent medical doctor) before inclusion. Informed consent will be obtained according to the Declaration of Helsinki.

There are two main modes of obtaining informed consent according to the different presentations of the patients: (1) Patients that are awake and have no cognitive impairment due to the cardiogenic shock will sign the informed consent prior to study initiation. A short and long version of the informed consent is available. (2) Patients with cognitive impairment due to the cardiogenic shock or that are sedated: two independent physicians will proof the presumed will of the patient. The patient will sign the consent form once he/she is recovered, or may not accept to be enrolled in the study and have to be excluded. Patients have the right to withdraw from study participation at any time without an explanation.

### 2.6. Objectives

#### 2.6.1. Primary Objective

The primary objective of the JenaMACS register is to investigate the potential benefit of the Impella CP^®^ on hemodynamics and left ventricular unloading in patients with cardiogenic shock after 24 h by using a ramp test protocol (Table 2 and Figure 1). The ramp test is performed as follows: During a step by step reduction of the Impella^®^ flow support (ramp test), hemodynamic (PCWP, SV) and echocardiographic parameters (left ventricular ejection fraction (LVEF), left ventricular end-diastolic diameter (LVEDD), and grading of mitral valve regurgitation) are recorded at each level from highest (P8) to lowest (P2). Measurements take place 10 min after adjusting the console to each flow level. In theory, mechanical assistance for unloading of the left ventricle might lead to a faster decrease in LVEDD, PCWP and mitral regurgitation and faster increase in LVEF and SV that could be translated into improved left ventricular recovery

#### 2.6.2. Secondary Objective

The secondary objectives are to gain information via serial hemodynamic measurements during Impella CP^®^ therapy in the time course, early from the start (10 min) to beyond 24 h, until explanation. Additionally, serial echocardiography will help to detect the effect of the Impella^®^ support to various echocardiographic parameters such as left heart size and right ventricular function. Apart from laboratory parameters, the secondary objectives mostly include clinical surrogate measures (e.g., mortality, time to lactate normalization intensive care unit (ICU) stay or time of mechanical ventilation) to identify or confirm potential advantages of Impella CP^®^ during the therapy and follow-up phase. Moreover, safety data like major and minor bleedings, stroke, sepsis and acute limb ischemia requiring intervention or surgery will be evaluated. Data acquisition during hospitalization and follow-up is displayed in Table 3.

### 2.7. Endpoints

The primary endpoint of the JenaMACS register study is the change in hemodynamic and echocardiographic parameters after 24 h during the ramp test at different Impella^®^ support levels. Parameters to be measured are listed in Table 2 and a scheme is provided in Figure 2. Secondary endpoints are listed in Table 4.

### 2.8. Time Schedule, Study Duration and Frequency of Study Visits

The study duration is planned for 60 months: 57 months of recruitment, 3 months for final follow-up and another 3 months for data analysis and publication. Table 3 outlines the study visits. The primary endpoint is measured after 24 h by using a ramp test (Table 2 and Figure 2). Follow-up of the patients is 12 months in total after the beginning of the Impella CP^®^ implantation.

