BGA including lactate	X	X	X	X	X	X				
Creatinine clearance **	X		X	X	X					
Blood Samples (Measurement of biomarkers)	X	X	X	X	X	X	X	X	X	X
PAC—Hemodynamics	X	X	X	X	X	X				
Measurement of parameters of hemodynamics ^∆^	X	X	X	X	X	X				
TTE	X	X	X	X	X	X	X	X		
Dose of isotopes and vasopressors	X	X	X	X	X	X	X	X		
Impella CP^®^ data	X	X	X	X	X	X				
SAPS-II Score		X	X	X	X	X				
CCS category								X	X	X
NYHA category								X	X	X
Quality of Life (EQ-5D)							X	X	X	X
Measurement of the neurological outcome (GCS) ^∆^	X	X	X	X	X	X	X	X	X	X

^∆^ Data documentation from clinical routine (if available), * every day until hemodynamic stabilization; ** Clearance calculated according to Cockcroft-Gault formula; ^+^ after Impella explantation; SAPS = Simplified Acute Physiology Score; ECG = Electrocardiography; TTE = Transthoracic echocardiogram; PAC = Pulmonary artery catheterization; NYHA = New York Heart Association; CCS = Canadian Cardiovascular Society; GCS = Glasgow coma scale; PCI = Percutaneous, coronary intervention; BGA = Blood gas analyses. EQ—5D = EuroQol questionnaire.

**Table 4 jcm-11-04623-t004:** Secondary endpoints of the JenaMACS study.

Secondary Endpoints
- Change of hemodynamic and echocardiographic parameters after 10 min, 30 min and every 8 h of Impella support - Need, type, dose and duration of inotropic/vasopressor treatment. - Time until hemodynamic stabilization (lactate < 2 mmol/L; mean arterial pressure > 65 mmHg) after implantation. - Change in inflammatory parameters over time. - Mean and area under the curve of serum-lactate measured every 8 h for 48 h after implantation. - Mortality defined as mortality rate in the hospital or anywhere after discharge, within 12 months after implantation. - Changes in kidney function after implantation. - Need and duration of renal replacement therapy (CVVHD) and mechanical ventilation after implantation. - Length of stay at ICU after implantation. - Need for an active assist device or heart transplantation after implantation. - SAPS II Score at baseline and every 24 h during Impella CP^®^ support. - EQ-5D-questionnaire including EQ VAS after implantation. - Neurological outcome (GCS) after implantation. - Safety aspects such as major bleeding according to GUSTO/BARC definition, critical limb ischemia, sepsis, hemorrhagic or ischemic stroke

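### Three months of final follow-up after 57 months of recruitment cannot deliver the 12-month follow-up and 12-month mortality endpoint that the same plan promises for every patient

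*Protocol article*

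**What the plan says.** Section 2.8 of the protocol article sets the calendar: the study is "planned for 60 months: 57 months of recruitment, 3 months for final follow-up and another 3 months for data analysis and publication". The end of the same section sets the observation time per patient: "Follow-up of the patients is 12 months in total", counted from implantation.

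Two tables rely on the 12-month figure:

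- **Table 3** has columns for 6 and 12 months, with physical examination, biomarker samples, CCS, NYHA, EQ-5D and GCS marked in both. After day 7 the only other visit is at 30 days. No visit falls at 3 months.
- **Table 4** lists, among the secondary endpoints, "Mortality defined as mortality rate in the hospital or anywhere after discharge, within 12 months after implantation".

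Section 2.11.2 plans Kaplan-Meier estimates and a log-rank test for time-to-event endpoints and Cox regression for long-term survival. It also limits secondary analysis to patients whose data for the endpoint in question are complete. Section 2.11.1 plans for 20 patients, and Section 2.14 expects under 4% loss to follow-up. Nowhere does the article say that late recruits are followed for less time or are censored at study end.

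**The concern.** The calendar and the per-patient follow-up cannot both be carried out. A patient enrolled at the end of recruitment has 3 months under observation, not 12. Four late outcomes depend on the missing time: 12-month mortality, and EQ-5D, NYHA and CCS at 6 and 12 months. GCS, the examination and the blood samples at those visits are lost as well.

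The risk is bias as well as missing data. A late recruit who dies before the cut-off has a known 12-month outcome; a late recruit who is alive at the cut-off does not. If mortality is reported as a simple rate under the complete-data rule of Section 2.11.2, the deaths stay in and the survivors drop out, which pushes mortality up. If unfinished follow-up is counted as survival, mortality is pushed down. With 20 patients, each unresolved patient is 1/20 = 5 percentage points.

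**Working it through.** **Inputs.** From Section 2.8: total 60 months, recruitment 57, final follow-up 3, analysis and publication 3, follow-up per patient 12. From Section 2.11.1: 20 patients. From Section 2.14: loss to follow-up below 4%. From the Introduction: mortality in cardiogenic shock of 30–70%, with no time horizon given. The accrual pattern is not given; uniform accrual over 57 months is assumed and then varied.

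**1. The stated total.**
- Recruitment + final follow-up = 57 + 3 = 60. This matches if analysis comes after the 60 months.
- All three listed items = 57 + 3 + 3 = 63. This does not match if analysis is part of the 60 months.

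**2. Calendar needed for 12 months per patient.**
- Last possible entry + follow-up = 57 + 12 = month 69.
- With 3 months of analysis: 69 + 3 = month 72.

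**3. Latest entry that still reaches each visit.** Latest entry = end of follow-up − visit time. Share short = (57 − latest entry)/57.

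| End of follow-up | Visit | Latest entry | Recruitment months short | Share | Expected of 20 |
|---|---|---|---|---|---|
| Month 60 | 12 months | 60 − 12 = 48 | 9 | 9/57 = 15.8% | 3.2 |
| Month 60 | 6 months | 60 − 6 = 54 | 3 | 3/57 = 5.3% | 1.1 |
| Month 63 | 12 months | 63 − 12 = 51 | 6 | 6/57 = 10.5% | 2.1 |
| Month 63 | 6 months | 63 − 6 = 57 | 0 | 0% | 0 |

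The month-63 rows are the most generous case, in which follow-up continues through the analysis period.

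**4. Sensitivity to accrual.** Uniform accrual is 20/57 = 0.35 patients per month. If the rate in the last 9 months were half of that, 0.5 × 3.2 = 1.6 patients would fall short of 12 months; if double, 2 × 3.2 = 6.3 (from the unrounded 3.16). If all 20 were enrolled by month 48, nobody would, but the plan allows entry until month 57. With independent uniform entry times, the chance that at least one patient falls short is 1 − (1 − 9/57)^20 = 97% for an end at month 60, and 1 − (1 − 6/57)^20 = 89% for an end at month 63.

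**5. Unknown 12-month mortality.** Deaths before the cut-off are known outcomes. If 30–70% of the late recruits die, and do so before the cut-off (an assumption), the number with unknown status is 3.2 × 0.3 = 0.9 to 3.2 × 0.7 = 2.2, so about 1 to 2 of 20.

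**6. Illustration of the bias.** Take the midpoint mortality, (30 + 70)/2 = 50%, or 10 deaths in 20. With two late survivors dropped as incomplete, the rate becomes 10/(20 − 2) = 56% instead of 10/20 = 50%.

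**The case against.** Much of what can be said in defence of the plan is right, and it limits the point.

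- **The sum.** A reader might infer that the timetable is a plain addition error, 63 against 60. The text does not support that firmly. Analysis and publication are introduced as a further 3 months, which can lie after the 60, and then 57 + 3 = 60 is correct. This is an ambiguity to clear up.
- **Survival methods.** A reader might infer that the survival analysis is spoiled. Kaplan-Meier and Cox handle administrative censoring, and Section 2.11.2 already names both. What stands is that Table 4 words mortality as a rate within 12 months, that no rule for late entry is given, and that censoring methods do not supply 12-month EQ-5D, NYHA or CCS values.
- **Size.** A reader might set 16% against the expected loss below 4% and call it four times too high. The two figures measure different things: the 4% in Section 2.14 is taken from other shock studies and is not a calendar cut-off. In this study 4% is 0.04 × 20 = 0.8 of a patient.
- **What is complete.** It is tempting to say that only 30-day outcomes are complete for all. Thirty days is the last scheduled visit that everyone reaches, but with recruitment ending at month 57 and follow-up at month 60, vital status can be obtained to about 3 months for every patient.
- **Importance.** The primary endpoint is the ramp test at 24 h, the study is a single-arm proof of concept, and the secondary endpoints are analysed descriptively. No primary conclusion depends on the 12-month data.

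None of this reconciles 3 months with 12. Nor is it detail that an article leaves to the full protocol, since both figures are stated in one section.

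**Conclusion.** The conflict is real and holds whether follow-up stops at month 60 or month 63: the calendar in Section 2.8 is incompatible with the 12-month follow-up in that section, the visits in Table 3 and the mortality endpoint in Table 4. Under uniform accrual about 3 of 20 patients (2 at best) cannot complete 12 months, and about 1 (none at best) misses the 6-month visit. The number with unknown 12-month mortality is smaller, about 1 to 2 if follow-up ends at month 60 and the deaths among late recruits fall before the cut-off. These counts rest on the assumed accrual; the contradiction does not. Severity is moderate, because only secondary endpoints are affected and the 24 h primary endpoint is untouched.

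**What to change.** Amend Section 2.8 in one of three ways, and say in the same edit whether the 60 months include the 3 months of analysis.

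1. **Keep 57 months of recruitment.** State the last visit at month 69 and analysis to month 72. Cost: follow-up ends 69 − 60 = 9 months later, and reporting moves back by about the same.
2. **Keep month 60 as the last visit.** Close recruitment at month 48, or at month 60 − 12 − 3 = 45 if analysis must also fit within the 60 months. Cost: a recruitment window shorter by 9 or 12 months, with a risk of enrolling fewer than 20 patients.
3. **Keep the calendar as it is.** State that late recruits are administratively censored and that 12-month mortality is a Kaplan-Meier estimate, not a crude or complete-case rate. State also that the 6- and 12-month visit data (EQ-5D, NYHA, CCS, GCS) will be incomplete by design, and that vital status is complete for all patients only to about 3 months. Cost: no delay, but fewer late outcomes.

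Each is a short text change. The first keeps both the recruitment window and all 12-month endpoints.

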### 2.9. Technology to Be Used

#### 2.9.1. Impella^®^

The Impella CP^®^ (Abiomed, Danvers, MA, USA) used for JenaMACS is an axial, non-pulsatile, continuous 14 Fr magnetic levitation propeller pump delivering a maximum flow of 3–4 L per minute. Inserted percutaneously via Seldinger technique, the Impella^®^ is then advanced retrograde from the common femoral artery, through the aorta and across the aortic valve into the LV. An ultrasound-assisted puncture of the femoral artery can be performed to minimize access site complications. The device is using an impeller to eject blood from the left ventricle into the ascending aorta via a tube. The pump is not dependent on pulsatile flow or EKG. The impeller speed defines the flow rate of the device and therefore the blood volume to be ejected. Maximal flow rate for ImpellaCP^®^ is 3.5 L/min. Flow rate adjustments can be set manually from an external console and are the basis of the ramp test 24 h after Impella CP^®^ implantation (Table 2 and Figure 2). Flow rate also depends on the preloading of the left ventricle.

